### Participants

#### Inclusion and exclusion criteria

The inclusion criteria for individuals with SCI were as follows: (a) 18–75 years old, right-hand dominant (Edinburgh Handedness Inventory); (b) diagnosed with SCI [15]; (c) stable MEP in the M1 hand area was detectable; (d) no cognitive impairment (Mini-Mental State Examination score ≥ 24) [16]; (e) disease course ≤ 1 month (from SCI onset to first assessment); and (f) agreed to participate in this study and signed the informed consent form. Exclusion criteria: (a) serious nervous system disease, unable to tolerate relevant tests; (b) upper limb fracture, arteriovenous fistula or other diseases leading to movement disorder; (c) ferromagnetic implants in the head or neck; (d) implantation of a cardiac pacemaker; (e) severe coagulation disorder, severe cardiac insufficiency or uncontrollable hypertension: systolic blood pressure > 160 mmHg or diastolic blood pressure > 100 mmHg; (f) other serious systemic diseases such as tumors; (g) taking drugs that may affect the TMS examination within a week, including baclofen, diazepam and other drugs [17]; (h) absolute contraindications for TMS examination.

The inclusion criteria for healthy controls were as follows: (a) 18–75 years old, right-hand dominant (Edinburgh Handedness Inventory); and (b) stable MEPs. Exclusion criteria included the above situations in which TMS could not be performed.

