### Outcome measures

#### Primary outcome

##### spTMS

To evaluate the changes in the M1 hand area CSE between individuals with SCI and healthy controls, the amplitude of the MEP and the resting motor threshold (RMT) will be detected through spTMS equipment (MEP-9404 C, Japan).

The MEP of the M1 hand area was recorded by the magnetic stimulation coil placed in the M1 hand area on the left side of the skull. The recording surface Ag-AgCl electrode and reference electrode were pasted on the abdomen of the abductor pollicis brevis muscle of the right hand and connected to the recording equipment. A single-pulse TMS is delivered to the hotspot under 80% of the maximum stimulator output. The MEP latency and amplitude of the abductor pollicis brevis muscle were recorded. RMT is defined as the minimal amount of stimulus intensity producing MEP peak-to-peak ≥ 50 µV in at least 5 out of 10 consecutive tracks [19]. The protocol used for the right M1 hand area was the same as that described above (Fig. 1A).

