#### ASIA impairment scale (AIS) grade

The AIS grade [23] mainly determines the degree of SCI (complete/incomplete injury) and can be divided into five scales: A, B, C, D and E. A indicates complete injury, B-D indicates incomplete injury, the degree of injury decreases successively, and E indicates normal sensorimotor function (Supplemental Table 3).

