#### Correlation analysis and multiple linear regression analysis

Correlation analysis of hemispheric excitability conversion degree and overall functional recovery was performed to determine the effects of disease course, AIS grade, and neurological level of injury. Pearson correlations between different phases/groups were calculated after the normality test. **P* < 0.05 is regarded as a significant difference.

Univariate and multivariate linear regression analyses will be conducted to validate the influence of hemispheric excitability conversion degree as an independent factor. The MBI and SCIM are set as the linear regression analysis outcomes. The inclusion criterion for univariate analysis was *P* < 0.10. **P* < 0.05 is regarded as a significant difference.

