Based on our previous retrospective research, a correlation analysis of hemispheric excitability conversion degree and overall functional recovery was performed to investigate the effects of neurological level of injury, disease course and AIS grade. The results showed a completely different correlation tendency in patients in the SCI subgroup. Among patients with different degrees of neurological injury, patients in the noncervical injury group had a significantly positive correlation with the degree of hemispheric CSE conversion and ability to perform ADL ability, while a nonsignificant positive correlation was found in the cervical injury group. This finding may be due to the influence of cervical injury on the UE CST pathway. In patients with AIS A, the degree of hemispheric CSE conversion was significantly positively correlated with the ability to perform ADLs, while no correlation was observed in AIS non-A patients. We further observed and confirmed changes in the cortical excitability of the M1 hand area under different influencing factors over a long period of time through a prospective cohort study.

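### The hand-MEP entry rule probably links AIS grade to injury level among enrolled patients, so correlations split by one factor at a time cannot tell which factor is responsible

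*Protocol article*

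**What the plan says.** All references are to the protocol article.

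- **Inclusion and exclusion criteria:** an SCI patient qualifies only if a "stable MEP in the M1 hand area was detectable". No limit or quota is set by injury level or AIS grade.
- **spTMS:** the MEP is taken from a hand muscle, with the electrode "pasted on the abdomen of the abductor pollicis brevis muscle of the right hand". The right hemisphere is handled the same way.
- **ASIA impairment scale (AIS) grade:** "A indicates complete injury, B-D indicates incomplete injury".
- **Correlation analysis and multiple linear regression analysis:** the correlation of conversion degree with functional recovery "was performed to determine the effects of disease course, AIS grade, and neurological level of injury". The method is given as "Pearson correlations between different phases/groups were calculated after the normality test". Univariate and multivariable linear regressions for MBI and SCIM follow, to test conversion degree as an independent factor. Neither AIS nor level is named as a covariate or modifier.
- **Discussion:** the team's earlier results are reported as two separate splits. By level, the correlation was significant in non-cervical patients and positive but non-significant in cervical patients; the authors comment that "This finding may be due to the influence of cervical injury on the UE CST pathway". By AIS, "In patients with AIS A, the degree of hemispheric CSE conversion was significantly positively correlated with the ability to perform ADLs", with no correlation in the other grades. The cohort is presented as following up these influencing factors over a longer period.

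**The concern.** Entry depends on a signal that travels from cortex to hand muscle. By the authors' own account, cervical injury can affect that pathway, and it is reasonable to expect the effect to be greatest when the injury is complete. A complete injury below the cervical cord is not selected against in this way. The rule therefore tends to thin out one cell of the level-by-AIS table, cervical AIS A. That leaves AIS A patients more often non-cervical than the rest.

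If the conversion-function relation depends only on level, a split by AIS will then show a stronger correlation in AIS A, although AIS plays no part. The reverse also holds: a pure AIS effect will appear as a level effect. Testing AIS formally, but alone, keeps the same bias, so this is a separate matter from the absence of an interaction test.

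What is at stake is the study's statement about which patients the marker works in, which could be attached to the wrong factor.

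**Working it through.** **Sample size available.** The plan's 25 per group reproduces. With P1 = 0.70, P2 = 0.26, mean 0.48, two-sided 5% and 90% power:

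n = [1.96·√(2·0.48·0.52) + 1.282·√(0.70·0.30 + 0.26·0.74)]² / 0.44² = (1.385 + 0.813)² / 0.1936 ≈ 25.

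25 × 1.2 = 30. So 25 to 30 SCI patients are available for every subgroup correlation.

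**Assumed inputs (not in the documents).** Before entry, 50% are cervical and 40% are AIS A at each level. A fraction q of cervical AIS A patients has a detectable hand MEP; everyone else enters. True r is 0.6 in non-cervical patients and r_c in cervical patients. AIS has no effect. Marker and outcome are standardised alike in every cell, so a group's slope equals its correlation and a mixed group's r is the weighted mean.

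**Cells before entry:** cervical A 0.20, cervical non-A 0.30, non-cervical A 0.20, non-cervical non-A 0.30.

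**q = 0.** The total enrolled is 0.80, so the mix is 0%, 37.5%, 25% and 37.5%. AIS A is all non-cervical; non-A is half cervical.
- r_c = 0: AIS A 0.60; non-A 0.5·0.6 + 0.5·0 = 0.30; false difference 0.30.
- r_c = 0.3: AIS A 0.60; non-A 0.5·0.6 + 0.5·0.3 = 0.45; false difference 0.15.

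**q = 0.25.** Cervical A is 0.05, so AIS A is 0.05/0.25 = 20% cervical.
- r_c = 0: AIS A 0.8·0.6 = 0.48; non-A 0.30; difference 0.18.
- r_c = 0.3: AIS A 0.48 + 0.06 = 0.54; non-A 0.45; difference 0.09.

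**q = 1.** Both AIS groups are half cervical; difference 0.

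**Other cervical shares.** With q = 0 and r_c = 0, a pre-entry cervical share of 40% to 60% puts non-A at 0.36 to 0.24, a false difference of 0.24 to 0.36.

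**The reverse case.** Suppose only AIS matters (r = 0.6 in A, 0 otherwise) and q = 0. Non-cervical patients are 25/62.5 = 40% AIS A, giving r = 0.24; cervical patients give 0. A level difference of 0.24 appears although level has no effect.

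**Simulation at n = 25 (same assumptions).**

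| q | r_c | Mean false AIS slope difference, AIS alone | AIS A significant, non-A not |
|---|---|---|---|
| 0 | 0 | 0.31 | 22% |
| 0 | 0.3 | 0.15 | 14–15% |
| 1 | 0 | 0.00 | 12% |
| 1 | 0.3 | about 0 | 16% |

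For q = 0 and r_c = 0, adding level and level × conversion to the model cuts the mean false difference from 0.31 to about 0.005. The SD of the estimate rises from 0.54 to 0.60, and the false AIS interaction is declared significant in 3.4% of studies instead of 8.0%.

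**Why the planned regression does not supply this.** As described, it tests the main effect of conversion degree. Even with AIS and level as covariates, a main-effects model does not show which of them changes the conversion-function slope.

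**The case against.** The strongest reply is that the premise is not measured. The documents give no AIS-by-level table, no cervical share and no count of patients excluded for an absent MEP. A reader might infer that the entry rule removes most complete cervical injuries, that enrolled AIS A patients are nearly all non-cervical, and that the study will report a false AIS effect. The documents support none of these. They support only that selection against cervical AIS A is plausible, and the bias is zero if AIS A is equally common at both levels.

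The size is also sensitive. Cervical r = 0 is harsher than the positive, non-significant correlation in the Discussion; at 0.3 the bias halves, and the significant-in-A-only pattern is no more frequent than its background. Even in the extreme case noise dominates: total error is √(0.31² + 0.54²) = 0.62 with AIS alone, against 0.60 jointly.

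Nor do the earlier results prove aliasing. A pure level effect predicts a positive correlation in non-A patients (0.30 to 0.45 above), whereas none was reported. The article also does not say that the earlier study used this entry rule.

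Finally, one-factor analysis is the natural reading of the methods and Discussion rather than an explicit statement, and interaction terms are often left to an analysis plan. These subgroup correlations are not the primary outcome.

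All of this limits the claim but does not remove it. The article does state the entry rule, the grouped Pearson method and the aim of determining the effects of both factors. In that combination, the stated method cannot separate them.

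**Conclusion.** The point holds as one of attribution. Selection on a hand MEP makes an association between AIS grade and level likely, and separate grouped correlations cannot then assign a difference to one or the other.

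Under the stated assumptions the false AIS difference ranges from 0 (no selection) to about 0.30 (no cervical AIS A enrolled, cervical r = 0), with 0.09 to 0.18 in between if a quarter of cervical AIS A patients enter. The evidence lies in the biased estimates. The frequency of the full significant/non-significant pattern (14–22% with no cervical AIS A, against a 12–16% background) adds little, because small subgroups alone produce most of it. This is worth correcting, but it does not threaten the study's primary comparison.

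**What to change.** In the correlation and regression section:

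1. Estimate conversion × AIS and conversion × level together in one model for each functional outcome. Give the AIS contrast within non-cervical patients as a supporting analysis.
2. Report the AIS-by-level table of enrolled patients and the number screened out for an absent hand MEP.
3. State that no conclusion on AIS within cervical injury will be drawn if that cell is nearly empty. With q = 0.25 it would hold about 25 × 0.05/0.85 ≈ 1.5 patients.
4. Label these analyses exploratory.

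This changes analysis and reporting text and needs no new assessments, beyond keeping a screening count. The price is a somewhat less precise AIS contrast (SD about 0.60 against 0.54 at n = 25). The within-non-cervical comparison would be small, about 6 AIS A against 9 other patients at n = 25 with q = 0, so it can support the joint model but not settle the question.

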**Methods:**

This study is a 12-month prospective cohort study. The neurophysiological and overall functional status of the participants will be assessed. The primary outcomes included single-pulse and paired-pulse TMS. The second outcome included functional near-infrared spectroscopy (fNIRS) measurements. Overall functional status included total motor score, modified Ashworth scale score, ASIA Impairment Scale grade, spinal cord independence measure and modified Barthel index. The data will be recorded for individuals with SCI at disease durations of 1 month, 2 months, 4 months, 6 months and 12 months. The matched healthy controls will be measured during the same period of time after recruitment.

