#### Motor score (MS)

The MS mainly evaluates the strength of key muscles innervated by different spinal nerves. The total score is 100, consisting of the upper extremity MS (UEMS) and lower extremity MS (LEMS) (Supplemental Table 1).

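### Subgroup Pearson correlations for motor score are not comparable across AIS grade and injury level, because the score or one of its halves has little range in some of those groups

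*Protocol article*

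**What the plan says.** Under Correlation analysis and multiple linear regression analysis, the protocol article correlates the conversion degree with overall functional recovery, an analysis that "was performed to determine the effects of disease course, AIS grade, and neurological level of injury". The tool is named: "Pearson correlations between different phases/groups were calculated after the normality test".

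Motor score is in scope. The abstract's Methods state: "Overall functional status included total motor score, modified Ashworth scale score, ASIA Impairment Scale grade, spinal cord independence measure and modified Barthel index". The Motor score (MS) section gives a 100-point total made up of UEMS and LEMS, and the Discussion values that split because it separates arms from legs.

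Of AIS grade the article says: "A indicates complete injury, B-D indicates incomplete injury, the degree of injury decreases successively, and E indicates normal sensorimotor function". No motor-score value is attached to any grade. Patients may enter only if a "stable MEP in the M1 hand area was detectable".

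The regressions in the same section do not use motor score: "The MBI and SCIM are set as the linear regression analysis outcomes". The Discussion reports earlier subgroup correlations for ADL only: significant in AIS A and in non-cervical injury, absent in AIS non-A, and positive but not significant in cervical injury.

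**The concern.** Pearson r measures association relative to the spread of both variables. Two groups with the same underlying relation will show different r values if the outcome varies widely in one and hardly at all in the other. AIS grade and neurological level are themselves descriptions of how much motor function is preserved, so grouping on them changes the spread of the motor score.

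At stake is the reading of the result. The Discussion treats earlier subgroup correlations (significant in one group, not in another) as a different tendency between groups. Applied to motor score, that reading could attribute to AIS grade or level what the range of the scale produces. Collecting more patients would not remove this.

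**Working it through.** **Stated figures.** The article gives no figure for this analysis. Its only computed figure is the sample size, which compares two proportions (0.70 and 0.26, two-sided 5%, 90% power): n = [1.960·√(2·0.48·0.52) + 1.2816·√(0.21 + 0.1924)]² / 0.44² = 24.9, so 25 per group. It reproduces, and becomes 30 per group after the 20% increase. It does not size any correlation.

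**Where the range is lost.** Assumptions, since the supplementary scoring table is not shown: UEMS and LEMS each run 0-50, each bilateral key-muscle segment carries 10 points, and strength in complete injury is normal above the level and zero below it.
- Non-cervical injury: UEMS is about 50.
- AIS A above the lumbar levels: LEMS is about 0.
- Both together (thoracic AIS A): total about 50 + 0 = 50.
- AIS A at all levels: the total follows level, from 0 at C4 to 50 at T1-L1 and higher below.

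SD of total motor score in AIS A under assumed level mixes:
- 50% spread evenly over C4-C8, 50% T1-L1: mean 35, SD 18.0
- 30% cervical, 60% T1-L1, 10% L2-L3: mean 42.5, SD 17.3
- 10% C8, 85% T1-L1, 5% L2: mean 49.5, SD 3.8
- T1-L1 only: SD 0

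**Effect on r.** Range-restriction formula, treating the grouping as direct selection on motor score (an approximation): r′ = r·u / √(1 + r²(u² − 1)), where u is the subgroup SD divided by the reference SD. Assumed r = 0.5. The chance of P < 0.05 is from Fisher's z at an assumed n of 12.

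| u | r′ | Chance of P < 0.05, n = 12 |
|---|---|---|
| 0.1 | 0.06 | 5% |
| 0.3 | 0.17 | 8% |
| 0.5 | 0.28 | 14% |
| 0.7 | 0.37 | 22% |
| 1 | 0.50 | 38% |

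Worked line for u = 0.3: 0.15 / √(1 + 0.25·(0.09 − 1)) = 0.15 / √0.7725 = 0.17.

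With an assumed whole-cohort SD of 20-25, the mix with SD 3.8 gives u = 0.15-0.19 and r′ = 0.09-0.11. The mix with SD 18 gives u = 0.72-0.90 and r′ = 0.38-0.46. At SD 0, r does not exist.

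**Do slopes cure it?** Only partly. Under the same direct selection on the outcome, the slope is multiplied by u² / (1 − r²(1 − u²)). At u = 0.28 and r = 0.5 this is 0.0784 / 0.7696 = 0.10, so a standardised slope of 0.50 falls to 0.05. Slopes are robust to a narrow predictor, not to an outcome at floor or ceiling.

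**The case against.** A reader might infer that motor score is constant by definition throughout AIS A, so that the analysis is bound to show no association there. The documents do not support that. AIS A is defined only as complete injury, the total then depends on level, and with mixed levels r falls only from 0.5 to about 0.37-0.46. Near-constancy needs a level of about T1-L1 as well. The entry rule favours that mix, because the hand response is recorded from a thumb muscle and ln(DH/NDH) needs a response from both hemispheres. How strongly it does so is not stated.

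A reader might also infer that the earlier ADL pattern could be reversed by the scale. A floor or ceiling in motor score cannot alter a correlation with MBI or SCIM, no loss of range is shown for either, and the earlier ADL correlations were significant in AIS A and in non-cervical injury.

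Other fair points:
- **The normality test comes first.** Near-constant scores would normally fail it. That catches the extreme case; milder restriction may pass.
- **UEMS and LEMS are already separated.** True, but the plan does not say which is used in which subgroup.
- **Small groups alone make nulls likely.** At r = 0.5 without any restriction, the chance of P < 0.05 is 31% at n = 10, 48% at n = 15 and 81% at n = 30. This stands as a separate problem.
- **An unseen analysis plan may settle the choice of component.** Possibly, but the article itself fixes subgroup Pearson r as the way to judge these factors.

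**Conclusion.** The point holds for motor score and its components. UEMS in non-cervical injury and LEMS in AIS A above the lumbar levels have little or no range, and total motor score is near constant where AIS A and a thoracic level coincide. There, r or its significance cannot show whether AIS grade or level changes the association.

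The size is uncertain. With r = 0.5 assumed, r′ runs from undefined, through 0.06-0.17 at SD ratios of 0.1-0.3, to 0.37 at a ratio of 0.7. Segment scoring, level mixes, SDs, r and subgroup size are all assumptions. The MBI and SCIM analyses are not shown to be affected. This is an improvement that should be made, not a flaw that undermines the study.

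**What to change.** In Correlation analysis and multiple linear regression analysis:

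1. Estimate the motor association in all SCI patients with AIS grade and neurological level in the model. State that a subgroup r for UEMS in non-cervical injury, or for LEMS in AIS A above the lumbar levels, will not be read as evidence of no association.
2. In non-cervical patients use LEMS, not UEMS or total motor score. Where UEMS is exactly at its maximum, the total is LEMS plus a constant and r is the same; the gain is that the label says what is being measured.
3. Judge the effects of AIS grade, level and disease course by a conversion-degree-by-group interaction, or by unstandardised slopes (points per unit of ln(DH/NDH)) with confidence intervals. Report the SD of outcome and predictor in each subgroup, and note that slopes also shrink where the outcome is at floor or ceiling.

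Motor correlations in AIS A need not be banned outright, since the score does vary with level there.

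The cost is a change of wording and a little more analysis on the same data. No separate motor estimate will be available where the score has no range, which the present plan could not supply either.

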### Monitoring of the safety and potential risks

TMS and fNIRS are noninvasive methods. During or after the procedure, some mild effects such as headache and dizziness may occur, which are normal reactions. If t symptoms occur, the doctor will actively treat and control them and seek assistance from relevant departments for diagnosis and treatment if necessary.

## Discussion

The present study is the first to analyze the role of bilateral M1 hand area excitability changes in the evaluation and prediction of overall functional recovery (including motor function and ADL ability) after SCI. In healthy people, the ppTMS-ICF of the DH is slightly greater than that of the NDH under physiological conditions, with no significant difference, confirming that both hemispheres generally maintain a stable status [28]. Ridding MC et al. confirmed that the DH side exhibited low-level short-interval intracortical inhibition, indicating the high excitability of DH [29]. Triggs WJ et al. also reported that the DH had a lower MEP threshold than the NDH, which suggested a high CSE in the DH [30]. In stroke, it is widely accepted that the stabilization of bilateral hemisphere excitability plays a vital role in motor rehabilitation. According to the interhemispheric inhibition model [31], the ‘overactive’ M1 of the unaffected hemisphere exhibits abnormally high interhemispheric inhibition compared with that of the affected hemisphere, impairing the recovery of the affected extremity. According to this model, one of our previous clinical study used the following protocol: the M1 hand area on the affected side with 10 Hz rTMS (excitation) and on the unaffected side with 1 Hz rTMS (inhibition). After intervention, patients showed significant improvement in motor function [32].

However, the changes in bilateral M1 excitability in individuals with SCI remain unclear, which limits targeted intervention for motor rehabilitation. To verify whether stable interhemispheric excitability in healthy people changes in individuals with SCI, we utilized spTMS (reflection of the CSE), ppTMS (reflection of intracortical excitability), and fNIRS (reflection of cortical blood flow) to assess changes in excitability and activation in the bilateral M1 hand area of individuals with SCI and its correlation with motor recovery/ADL ability.

Moreover, evaluating and predicting overall functional recovery (including motor function and ADL ability) after SCI is another target of this research. As discussed above, a recent study revealed that the M1 hand area of individuals with SCI encodes the activity information of both the UE and LE, and the movement coding of the UE and LE are highly correlated [9]. Similarly, Freund P et al. reported an increase in task-related activation in the paralyzed left M1 leg area during a right handgrip task in individuals with SCI, indicating structural associations between hand motor function and the M1 leg area [33]. In this view, the above studies support the opinion that M1 hand area and extremity motor function (including the UE and LE) are highly correlated. Therefore, changes in the hemispheric excitability of the M1 hand area may be used to assess extremity motor function and ADL ability, which could serve as potential indicators of overall functional recovery. Herein, we utilized the MS, the SCIM12 and the MAS for motor function evaluation and the MBI and SCIM for ADL ability assessment. The MS focuses on basic motor function. In addition, the total MS consists of the UEMS and LEMS, which is more convenient for distinguishing between the UE and LE. The SCIM12 evaluates the mobility of individuals with SCI indoors [25]. The MAS measures muscle tone. For ADL ability, the MBI is the most widely used scale and has been utilized to evaluate functional outcomes after SCI rehabilitation [34]. The SCIM focuses on individuals with SCI and has a relatively high sensitivity [35]. We utilize these two ADL assessment scales for mutual verification.

Based on our previous retrospective research, a correlation analysis of hemispheric excitability conversion degree and overall functional recovery was performed to investigate the effects of neurological level of injury, disease course and AIS grade. The results showed a completely different correlation tendency in patients in the SCI subgroup. Among patients with different degrees of neurological injury, patients in the noncervical injury group had a significantly positive correlation with the degree of hemispheric CSE conversion and ability to perform ADL ability, while a nonsignificant positive correlation was found in the cervical injury group. This finding may be due to the influence of cervical injury on the UE CST pathway. In patients with AIS A, the degree of hemispheric CSE conversion was significantly positively correlated with the ability to perform ADLs, while no correlation was observed in AIS non-A patients. We further observed and confirmed changes in the cortical excitability of the M1 hand area under different influencing factors over a long period of time through a prospective cohort study.

